## Abstract

**Background:**

Halitosis is a common problem that affects a large portion of the population worldwide. The origin of this condition is oral in 90% and systemic in 10% of cases. The unpleasant odor is mainly the result of volatile sulfur compounds produced by Gram-negative bacteria. However, it has recently been found that anaerobic Gram-positive bacteria also produce hydrogen sulfide (H_2_S) in the presence of amino acids, such as cysteine. Light, both with and without the use of chemical agents, has been used to induce therapeutic and antimicrobial effects. In photodynamic therapy, the antimicrobial effect is confined to areas covered by photosensitizing dye. The aim of the present study is to evaluate the antimicrobial effect of photodynamic therapy on halitosis in adolescents through the analysis of volatile sulfur compounds measured using gas chromatography and microbiological analysis of coated tongue.

**Methods/Design:**

A quantitative clinical trial will be carried out involving 60 adolescents randomly divided into the following groups: group 1 will receive treatment with a tongue scraper, group 2 will receive photodynamic therapy applied to the posterior two-thirds of the dorsum of the tongue, and group 3 will receive combined treatment (tongue scraper and photodynamic therapy). Gas chromatography (OralChroma^TM^) and microbiological analysis will be used for the diagnosis of halitosis at the beginning of the study. Post-treatment evaluations will be conducted at one hour and 24 hours after treatment. The statistical analysis will include the Shapiro-Wilk test for the determination of the distribution of the data. If normal distribution is demonstrated, analysis of variance followed by Tukey’s test will be used to compare groups. The Kruskal-Wallis test followed by the Student-Newman-Keuls test will be used for data with non-normal distribution. Either the paired *t*-test or the Wilcoxon test will be used to compare data before and after treatment, depending on the distribution of the data.

**Discussion:**

The results of this trial will determine the efficacy of using photodynamic therapy alone or in combination with a tongue scraper to treat bad breath in adolescents.

**Trial registration:**

The protocol for this study was registered with Clinical Trials (registration number NCT02007993) on 10 December 2013.

## Background

Halitosis is a term used to define an unpleasant odor that emanates from the mouth, stemming from either a local or systemic origin [1–3]. This common problem affects a large portion of the population worldwide and causes considerable embarrassment. Therefore, halitosis has a negative impact on social communication and quality of life [4]. The lack of standardization in the protocol for the diagnosis and treatment of halitosis hinders the comparison of data from epidemiological studies conducted in different countries and yet it is believed that 25% of the population are affected by this condition [5].

Studies on the etiology of halitosis report that 2% of cases stem from renal, metabolic, hepatic, endocrinological and gastrointestinal disorders (such as infection by *Helicobacter pylori* and intestinal blockage), and 8% are due to conditions of the respiratory system and conditions of the ears, nose and throat (ENT), such as acute tonsillitis, postnasal drip, sinusitis and tonsillolith. The majority of cases (80 to 90%) are directly linked to conditions of the oral cavity, such as periodontal disease, coated tongue, poor oral hygiene, salivary abnormalities (change in pH and hyposialy), stomatitis, intra-oral neoplasm, pulp exposure, extraction wounds and crowding of the teeth [5–8].

Bad breath mainly stems from volatile sulfur compounds (VSCs) produced by the action of anaerobic Gram-negative bacteria (*Fusobacterium nucleatum*, *Selenomonas*, *Treponema denticola*, *Prevotella intermedia*, *Tannerella forsythyia*, *Porphyromonas gingivalis*, *Bacteroides forsythus* and *Eubacterium*) found in the oral cavity on substrates containing sulfur [9–11]. The VSCs produced by the metabolism of these bacteria are hydrogen sulfide (H_2_S), found mainly on the dorsum of the tongue, methanethiol (CH_3_SH) in gingival pockets and dimethyl sulfide (CH_3_SCH_3_), which has an extra-oral origin [12–15]. The concentration of these compounds is used as an indicator of halitosis [3, 16].

Recently, the anaerobic Gram-positive bacterium *Solobacterium moorei* (also known as *Bulleidia moorei*) has been associated with halitosis due to the production of H_2_S in the presence of different supplements containing amino acids, especially cysteine [17, 18]. Studies have demonstrated that the presence of these bacteria on the dorsum of the tongue, as well as in saliva and periodontal pockets, can lead to both halitosis and systemic problems such as complications during pregnancy, cardiovascular disease and chronic lower respiratory infection [19], which is considered the third most common cause of death [2, 20–23].

### Detection

Two main methods are used to evaluate halitosis: a subjective (organoleptic) evaluation and an objective evaluation (quantitative measure of VSCs, gas chromatography (GC) and monitor analysis) [24–27]. Studies comparing the efficacy of these methods report GC to be the most objective and efficacious method for the individual detection of H_2_S, CH_3_SH and CH_3_SCH_3_, allowing the evaluation of both the intensity of bad breath and its origin [5, 15]. Indeed, GC is currently considered the gold standard for the detection of halitosis [11]. However, the majority of researchers have used a combination of both subjective and objective evaluations, whereas others have only used an organoleptic evaluation due to its ease of execution and low cost [24]. Halitosis can be analyzed using a sulfide monitor, such as the Halimeter (Interscan Corporation, Chatsworth, California, United States) [3, 4, 26–28], which determines the total amount of VSCs in parts per billion (ppb) under normal conditions.

### Photodynamic therapy

Photodynamic therapy (PDT) was discovered in 1900 by Oskar Raab and Hermann von Tappeiner. In the 1970s, PDT began to be used for the treatment of cancer. Recently, antimicrobial PDT has been used as a treatment option for localized infections [29]. PDT involves the use of a non-toxic light-sensitive photosensitizer combined with visible light at the appropriate wavelength to coincide with the absorption spectrum of the photosensitizer, which reaches a state of excitation after absorbing the photons, reacting with the oxygen in the medium to form reactive oxygen species. This phototoxic reaction induces the destruction of bacterial cells. The antimicrobial effect is confined to areas covered by the light-activated photosensitizer, quickly acting on the target organisms when the appropriate energy dose and output power are used [9, 29–33]. According to Wainwright [34], bacterial resistance to PDT is unlikely, as the singlet oxygen and free radicals formed interact with different bacterial cell structures and different metabolic pathways [32, 33].

The conventional treatment of halitosis related to oral conditions consists of the chemical reduction of microorganisms with a mouthwash, such as 0.2% chlorhexidine, essential oils, triclosan and hydrogen peroxide, the mechanical removal of nutrients with a tongue scraper or brush, the masking of odor with chewing gum, mints and breath spray, and the transformation of VSCs using zinc plus chlorhexidine [2, 5, 10, 12, 35–37]. However, the irregular characteristics of the surface of the dorsum of the tongue make the adequate reduction in bacterial a particular challenge [2, 36, 38].

Considering the scarcity of studies addressing the effect of PDT on tongue biofilm, the aim of the present study was to evaluate the effectiveness of PDT on the dorsum of the tongue in adolescents with halitosis by an analysis of VSCs and microbiological analysis of the tongue.

## Methods/Design

This study will be carried out in compliance with regulatory norms governing research involving human subjects. Approval was obtained from the Human Research Ethics Committee of University Nove de Julho (Brazil) under process number 037315/2013, and the study is registered with the United States National Institutes of Health (Clinical Trials.gov registration number: NCT02007993). The guardians of the participants will be informed regarding the procedures and will sign a statement of informed consent authorizing the participation of their sons and daughters in compliance with Resolution 196/96 of the Brazilian National Health Board.

Male and female adolescents enrolled at the dental clinic of the university will be recruited for the study. Those aged between 13 and 18 years, with a diagnosis of halitosis and OralChroma™ results of H_2_S ≥112 ppb during the cysteine challenge [11, 15, 39, 40] will be included. The exclusion criteria will be [41] dentofacial anomalies, currently undergoing orthodontic or orthopedic treatment, current use of a removable appliance, implant or dentures, periodontal disease, teeth with carious lesions, currently undergoing cancer treatment, diabetes mellitus, systemic (gastrointestinal, renal or hepatic disorder) conditions, ear, nose or throat conditions, respiratory conditions, antibiotic therapy in the previous month, current pregnancy [5] or hypersensitivity to the photosensitizer. As this is a randomized clinical trial, the recommendations of the Consolidated Standards of Reporting Trials (CONSORT) will be used to ensure greater transparency and quality (Figure 1).

**Figure 1 Fig1:**
[figure not shown]
**Flowchart of study.** P = output power; E = energy and T = time in seconds.

The subjects selected will be randomly allocated to three groups (Table 1). All individuals will be submitted to evaluations with OralChroma™ before and after treatment.

**Table 1 Tab1:** **Summary of experimental conditions**

Group	Halitosis	Treatment	
1	H_2_S ≥112 ppb	Tongue scraper	
2	H_2_S ≥112 ppb	PDT	
		E = 9 J	T = 90 s
3	SH_2_ ≥ 112 ppb	Tongue scraper + PDT	
		E = 9 J	T = 90 s

H_2_S = hydrogen sulfide; ppb = part per billion; PDT = photodynamic therapy; E = energy; T = time in seconds.

### Microbiological analysis

Microbiological analyses of coated tongue will be performed before and after treatment using a 1-μl inoculation loop for the collection of biofilm samples from the dorsum of the tongue. The samples will be transferred to 1.5-ml vials with reduced transport fluid and placed in a vortex mixer (Prolab, São Paulo – Brazil) for approximately 30 seconds for homogenization. Ten-fold serial dilution will be prepared in 180 μl of sterile phosphate buffered saline (Probac, São Paulo – Brazil) and aliquots of 10^−2^, 10^−3^, 10^−4^ and 10^−5^ will be transferred to plates with brain-heart infusion agar (Probac, São Paulo – Brazil). As the main bacteria responsible for the production of VSCs are Gram-negative, the plates will be incubated in anaerobic jar for 72 hours at 37°C, following by the quantification of colony-forming units [10, 42].

### Halitosis detection

The literature describes a number of methods for measuring halitosis, such as an organoleptic evaluation of the air emanating from the oral cavity [16, 26] using a sulfide monitor [16, 25, 43] or GC [11, 43, 44]. However, it has been demonstrated that the organoleptic test can be influenced by the olfactory capacity and emotional state of the examiner, as well as climatic conditions [3]. Therefore, the portable OralChroma™ device Abilit Corporation, Chuo-ku, Osaka - Japan) will be employed. This device uses a highly sensitive gas semiconductor sensor.

The participant will first rinse with cysteine (Fórmula & Ação, São Paulo – Brazil) for one minute (cysteine 10 mM - 16 mg of cysteine in 100 ml of distilled water - 16% mg). A syringe will be placed in the participant’s mouth with the plunger completely inserted. The participant will close his or her mouth, breathe through the nose and remain still with the mouth closed for one minute. The participant will be instructed not to touch the tip of the syringe with his or her tongue. The plunger will then be withdrawn, pushed back in to empty the air into the participant’s mouth and will be withdrawn again to fill the syringe with the breath sample. The tip of the syringe will be cleaned to remove saliva and a gas injection needle will be placed on the syringe. The plunger will be adjusted to 0.5 ml and the contents will be injected into the input of the device in a single motion (Figure 2) [15].

**Figure 2 Fig2:**
[figure not shown]
**Process for the acquisition of the sample for the halimetric.** OralChroma (Abiliti Corporation, Chuo-ku, Osaka – Japan). The OralChroma™ will be connected to the computer with a specific software program that allows the creation of a graph corresponding to the peaks and concentrations of VSCs (0 to 2913 ppb) with considerable precision after eight minutes. The results are stored in the program, as well as in the device itself, and can be retrieved at any time for comparisons of the readings before, during and after treatment.

### Analysis of VSCs

OralChroma™ (Abilit Corporation) was developed in Japan for the individual determination of H_2_S, CH_3_SH and CH_3_SCH_3_, allowing for the evaluation of both the intensity of bad breath and its origin [5, 11, 15]. H_2_S originates mainly from bacteria on the dorsum of the tongue. Values greater than 112 ppb indicate halitosis. CH_3_SH is found in greater concentration in periodontal pockets. Values up to 26 ppb are considered normal. Periodontal disease typically results in a high CH_3_SH:H_2_S ratio (>3:1). CH_3_SCH_3_ may have a periodontal or systemic (intestine, liver or lung) origin and may also be temporarily caused by the ingestion of certain foods and beverages. The distinction between CH_3_SCH_3_ of an oral or systemic origin can be made through the comparison of the results of the halimetric (OralChroma™) with and without a cysteine challenge. The perception threshold for CH_3_SCH_3_ is very low (8 ppb). Other non-VSC odors may appear in a peak prior to the theoretical first peak, which is H_2_S [15].

To maximize the standardization of the readings, the exam will be carried out in the morning and the participants will be instructed to avoid the ingestion of foods with garlic, onion or strong spices, as well as the consumption of alcohol and the use of an antiseptic mouthwash. On the morning of the exam, more than two hours should have passed since any food intake and the participants are to abstain from coffee, hard candy, chewing gum, oral hygiene products and personal care items containing fragrances (aftershave, deodorant, perfume and creams). Brushing will be performed with water alone [27, 45].

### Photodynamic therapy

The THERAPY XT-ES™ (DMC ABC Medical and Dental Equipment, São Paulo, Brazil) with a red (660 nm) and infrared (810 nm) laser and a fine tip (for regions of difficult access) will be used. Only the volunteer and operator will be present at the time of PDT and both will be wearing protective eyewear. The active point of the laser will be covered with disposable clear plastic wrap (PVC) for hygiene purposes and to avoid cross-contamination. The operator will use the appropriate clothing.

A single session of PDT will be performed with the Chimiolux™ methylene blue photosensitizer (DMC ABC Medical and Dental Equipment, São Paulo, Brazil) at a concentration of 0.005% (165 μm) applied to the middle and posterior thirds of the dorsum of the tongue. After five minutes of pre-irradiation time for incubation, the excess will be removed with an aspirator to maintain the surface moist with the photosensitizer alone (without the use of water). A total of six points will be irradiated (Figure 3). Based on studies developed for the treatment of periodontal disease with PDT [46–52] and a previous pilot study [53], the device will be calibrated with a wavelength of 660 nm, power output of 100 mW, fluency of 320 J/cm^2^, irradiance of 3537 mW/cm^2^ and an energy dose of 9 joules for 90 seconds per point in groups 2 and 3. The punctual application method will be used with the conventional tip in contact with the tongue (Table 2).

**Figure 3 Fig3:**
[figure not shown]
**Points of photodynamic therapy application.**

**Table 2 Tab2:** **Parameters of laser**

Parameter	Red laser
Center wavelength (nm)	660
Spectral bandwidth (FWHM) (nm)	5
Operating mode	Continuous wave
Average radiant power (mW)	100
Polarization	Random
Aperture diameter (cm)	0.094
Irradiance at aperture (mW/cm^2^)	3537
Beam profile	Multimode
Beam spot size at target (cm^2^)	0.02827
Irradiance at target (mW/cm^2^)	3537
Exposure duration (s)	90/120
Radiant exposure (J/cm^2^)	320/428
Radiant energy (J)	9/12
Number of points irradiated	9
Area irradiated (cm^2^)	0.254
Application technique	Contact
Number and frequency of treatment sessions	1 session
Total radiant energy (J)	81/108

### Tongue scraping intervention

A Halicare™ tongue scraper (Odomed, São Paulo, Brazil) will be used for the removal of biofilm. The participant will be instructed to divide the tongue into two parts and scrape each side 10 times (Figure 4).

**Figure 4 Fig4:**
[figure not shown]
**Diagram of tongue scraper use.**

### Calculation of sample size

The error was established as , in which  and  are the means of groups 1 and 2. Assuming both samples as having the same size (n_1_ = n_2_), the sample size is obtained from the following equation:
1

in which  and  are the variances in groups 1 and 2, respectively. As more than two groups will be studied, the decision was made to employ the largest error found in the literature [54] to estimate the sample size. Assuming all groups as having normal or approximately normal distribution, and that the sample will be large enough for a significance level of α = 0.05, the *Z* value was determined to be 1.96. However, for the sample size, the test power was established as 1-β = 0.80. In case the hypothesis of normality in the samples was rejected, the sample size was corrected by 5%. Based on the experimental groups in the study by Tsai *et al*. [54] it was determined that each group should contain 26 participants (n = 26).

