### Organization and statistical analysis of data

The Shapiro-Wilk test will be used to determine the distribution of the halimetricdata. If the data presents with normal distribution, analysis of variance (ANOVA) followed by the Tukey test will be used to evaluate the correlation between each of the proposed treatments and halitosis. The paired *t*-test will be used to compare the data before and after each treatment and determine whether the treatments reduced the degree of halitosis. The Kruskal-Wallis test followed by the Student-Newman-Keuls test will be used for data with non-normal distribution, and the Wilcoxon test will be used to analyze the data before and after each treatment. Microbiological data presents with log-normal distribution and will therefore be analyzed using the methods described for data with normal distribution. A significance level of α = 0.05 will be used.

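### Choosing the largest literature 'error' does not allow for three groups, and the stated 80% power does not carry over to the planned Tukey comparisons

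*Protocol article*

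**What the plan says.** All of the following is in the Protocol article.

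- **Calculation of sample size, formula.** An 'error' is defined from quantities that "are the means of groups 1 and 2". The equation that follows is for two equal groups ("Assuming both samples as having the same size") and uses terms that "are the variances in groups 1 and 2, respectively". The symbols themselves did not survive in the text available.
- **Calculation of sample size, choice of planning value.** "As more than two groups will be studied, the decision was made to employ the largest error found in the literature".
- **Calculation of sample size, error rates.** The sample is taken to be "large enough for a significance level of α = 0.05", the Z "value was determined to be 1.96", and "the test power was established as 1-β = 0.80". A 5% correction for non-normality is mentioned. The result is 26 per group. No numerical difference or SD is given, and no adjustment for multiple comparisons is described.
- **Organization and statistical analysis of data.** For normally distributed data, "analysis of variance (ANOVA) followed by the Tukey test will be used". Otherwise Kruskal-Wallis with Student-Newman-Keuls is planned. Before-after changes are tested by paired t-test or Wilcoxon test.
- **Abstract, Methods/Design.** The total is 60 adolescents in three groups, which is 20 per group if split equally. Three groups of 26 would be 78.

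**The concern.** There are two separate problems.

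First, the reason given for the planning value runs the wrong way. A third group adds comparisons and calls for a larger n. Taking the largest difference on record makes n smaller.

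Second, Z = 1.96 is the two-sided 5% value for one comparison, whereas three groups give three pairwise comparisons and Tukey's procedure uses a stricter critical value. The only allowance made for the third group is the largest-error choice, which does not help.

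At stake is what the 80% means. The Discussion expects to show that PDT is more effective, which is a between-group claim. A reader would take 80% as the chance of detecting such a difference in the planned pairwise tests, and it is lower than that.

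**Working it through.** **Inputs.** From the sample size section: alpha 0.05, Z = 1.96, power 0.80, equal groups, n = 26, a 5% correction. From the analysis section: three groups, Tukey. From the abstract: 60 in total. The difference, the SD and the printed equation are not available.

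**Step 1: direction.** The usual two-group formula is n = (var1 + var2)(z_alpha + z_beta)² / error². With equal variances and d = difference/SD, this is n = 2(1.96 + 0.84)² / d². Since n is proportional to 1/error², a larger error gives a smaller n. From a base of about 25, a difference 0.8 times as large needs 25/0.64 = 39.1, so 40 per group. One half as large needs 25/0.25 = 100 (101 after rounding at full precision). The direction is the same if 'error' means a margin of estimation.

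**Step 2: the plan's own figure.** Without the difference and SD, 26 can be neither confirmed nor refuted. The formula can be solved backwards: d = sqrt(2(1.96 + 0.84)² / n). It is unclear whether 26 already includes the 5%, so several bases were tried:

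| n before any correction | implied d |
|---|---|
| 26 (no correction) | 0.777 |
| 25 (× 1.05 = 26.25) | 0.792 |
| 24.76 (× 1.05 = 26.0) | 0.796 |
| 24 (lower bound) | 0.809 |

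At 26 per group, these give 80% to 83% power for one unadjusted comparison (normal approximation) or 78% to 82% (t-test). The stated 80% is therefore coherent for that single test.

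**Step 3: the same difference under Tukey.** The critical value is q(0.95; 3, 75)/sqrt(2) = 3.382/1.414 = 2.39. Power is from the noncentral t with 75 degrees of freedom and noncentrality d × sqrt(26/2), which is 2.80 to 2.92. At 20 per group the degrees of freedom are 57 and the critical value is 2.41.

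| True difference | Tukey power, 26 per group | Tukey power, 20 per group |
|---|---|---|
| implied d (0.78 to 0.81) | 66% to 70% | 52% to 56% |
| three quarters of it | 39% to 42% | 29% to 32% |
| half of it | 17% to 18% | 13% to 14% |

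The last two rows are illustrations at chosen fractions, not predictions. At 26 per group, Tukey reaches 80% only from a difference of about 0.90 SD. For 80% at the implied d it would need 32 to 35 per group.

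**Step 4: if the equation had no power term.** With Z alone, d = sqrt(2 × 1.96² / n), which is 0.54 to 0.56 for bases 26 to 24.76. Unadjusted power at 26 per group is then 50% to 52%, and Tukey power 34% to 36%.

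**Step 5: the overall F test.** Using the d values from step 2 at 26 per group, F-test power is 82% to 85% if one group differs and the other two are equal, and 69% to 73% if the third mean lies midway. At 20 per group the same patterns give 70% to 73% and 56% to 60%.

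**The case against.** Five counter-arguments deserve an answer.

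- **The equation is not readable.** This stands. Reading 'error' as a difference in means is an inference from its definition by two group means with variances entered separately. Every power figure depends on the assumed formula, which is why the version without a power term is shown too. Neither version brings a Tukey comparison to 80%.
- **The document never says that 80% applies to each Tukey pair.** True, and sizing on one pair is common practice. But the section names three groups as a reason for its choice and then makes no working allowance for them.
- **Other planned tests may be adequately powered.** The stated null hypothesis concerns change after PDT, for which paired tests are planned. If the before-after change equals the implied d and the correlation is 0.5 (both assumed), paired t-test power at 26 is 97% to 98%. With zero correlation it is 77% to 80%. The F test can also exceed 80%. This limits the point to the pairwise between-group comparisons.
- **Tukey applies only to normally distributed data.** Correct. The figures do not cover the Student-Newman-Keuls branch.
- **The contrasts of interest need not be small.** A reader might infer that PDT versus scraper, or combination versus PDT, must be smaller than the literature's largest difference. The document gives no effect size by contrast and does not say which contrast supplied the largest error, so it does not support that inference.

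A reader might also infer that Z = 1.96 was chosen because there are three groups. The text ties it to alpha = 0.05, and gives the number of groups as the reason for the largest error only.

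**Conclusion.** The point holds in two limited parts. The largest-error rationale is backwards as an allowance for more than two groups, on either natural reading of 'error'. And the calculation covers one unadjusted two-group comparison, while the normal-data analysis makes three Tukey comparisons.

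If 26 came from the usual formula with 80% power, the shortfall for a Tukey pair at the planning difference is about 10 to 14 percentage points at 26 per group and 24 to 28 at 20 per group. It is larger if the equation omitted the power term. These figures assume equal variances, normal data and the formula stated above.

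The documents do not support the stronger readings that 26 is an arithmetic error or that the trial as a whole is underpowered. The conflict between 60 in total and 26 per group is visible without the lost equation, and it decides which power figure applies.

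**What to change.** Rewrite the sample size paragraph as follows:

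1. Remove the statement that using the largest error deals with having more than two groups.
2. State the planning difference and SD taken from the cited study, and whether 26 includes the 5% correction.
3. Say that 80% refers to one unadjusted two-group comparison at that difference.
4. Reconcile 60 in total with 26 per group (3 × 26 = 78), so that one n is used throughout.
5. Report Tukey-adjusted pairwise power at that n, for the planning difference and for the smallest difference of interest.

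The cost is a recalculated paragraph and a less favourable stated power. Points 1 to 3 and 5 need no extra participants. Point 4 asks only that the intended number be stated consistently.

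### The abstract plans 60 adolescents in three groups, but the sample size section requires 26 per group (78 in all); if 60 is the operative size, the stated 80% power does not apply to it

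*Protocol article*

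**What the plan says.** The abstract of the protocol article, under Methods/Design, gives the trial size: "A quantitative clinical trial will be carried out involving 60 adolescents randomly divided into the following groups". It then lists three groups: tongue scraper, photodynamic therapy, and both combined. The main Methods/Design section confirms the number of groups: "The subjects selected will be randomly allocated to three groups (Table 1").

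The section Calculation of sample size treats the problem as a comparison of two means with equal group sizes: "Assuming both samples as having the same size (n_1_ = n_2"). It fixes the error rate ("significance level of α = 0.05, the *Z* value was determined to be 1.96") and the power ("for the sample size, the test power was established as 1-β = 0.80"). It adds an allowance: "In case the hypothesis of normality in the samples was rejected, the sample size was corrected by 5"%. Using results from a cited study, it ends with: "it was determined that each group should contain 26 participants (n = 26").

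The section does not print a total for the whole trial, and the abstract does not print a size per group. The article gives no dropout allowance, no unequal allocation ratio and no later revision of the target.

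**The concern.** Three groups of 26 make 78, and the abstract has 60. Both are statements of the current design, and neither comes from an amendment history. At least one of them is therefore wrong, or the link between them has been left out.

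The 0.80 power is attached to 26 per group. If recruitment stops at 60, the trial carries a power claim that belongs to a larger trial, and a null result would be read as coming from an 80%-powered comparison when it did not. Trial status says recruitment has begun, so the target has practical consequences now.

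**Working it through.** **Inputs**
- Total: 60 (Abstract, Methods/Design).
- Groups: 3 (Methods/Design; Table 1).
- Size per group: 26 (Calculation of sample size).
- Alpha 0.05 with Z = 1.96, hence two-sided; power 0.80, for which z = 0.842 (same section).
- Correction of 5% for non-normality (same section). It is unclear whether 26 is before or after it.
- Mean difference and variances: not available. The equation's symbols did not survive in the text at hand, and the values come from a cited study that is not shown.

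**Step 1. The totals.** 3 × 26 = 78. 78 − 60 = 18, and 18/78 = 23%. This step needs no assumption.

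**Step 2. Can anything in the article bridge the gap?**
- *The 5% correction.* 26/1.05 = 24.8 and 20 × 1.05 = 21, so it does not connect 20 with 26. An uncorrected base of 24 or 25 per group (24 × 1.05 = 25.2 and 25 × 1.05 = 26.25, either of which could be reported as 26) still needs 72 or 75 participants.
- *Unequal allocation.* No split of 60 gives three groups of 26. With the planning difference from step 3, a 26/26/8 split keeps power 0.80 for one comparison and gives 0.485 for the other two. A 26/17/17 split gives 0.70, 0.70 and 0.62.
- *Dropout.* None is stated, and an allowance would make enrolment larger than the required number, not smaller.

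**Step 3. What difference does 26 per group imply?** The 26 cannot be reproduced forwards, because the mean difference and variances are not visible. I therefore solve the usual two-sample formula backwards, with d the difference in SD units:

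n = 2 (1.960 + 0.842)² / d², so d = 2.802 × √(2/n)

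- If 26 is the plain 80% size: d = 2.802 × √(2/26) = 0.777. Put back in, this returns n = 26.
- If 26 includes the correction, base 25: d = 0.792.
- Same, base 24: d = 0.809.

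**Step 4. Power at 20 per group** (60/3, equal allocation). Power = Φ(d × √(20/2) − 1.960).

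| Base n for 80% power | d (SD) | d × √10 − 1.960 | Power at 20 per group |
|---|---|---|---|
| 26 | 0.777 | 0.497 | 0.690 |
| 25 | 0.792 | 0.546 | 0.707 |
| 24 | 0.809 | 0.597 | 0.725 |

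Using the noncentral t distribution both to find d and to evaluate power gives nearly the same answers: d = 0.792, 0.809 and 0.826, with power 0.685, 0.703 and 0.721.

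**Step 5. Difference detectable with 80% power at 20 per group.** d = 2.802 × √(2/20) = 0.886 SD. That is 14% larger than 0.777 (√(26/20) = 1.140) and 10% larger than 0.809 (√(24/20) = 1.095).

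**The case against.** The best case on the other side accepts the 60 versus 78 mismatch and limits what follows from it.

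- **The operative size is unknown.** Apart from the abstract, the only size given in the text is 26 per group. The flowchart (Figure 1) is not shown and may carry group sizes. The fault may be no more than an abstract that was not updated, with power intact. A reader might infer that the trial is underpowered. The article does not establish that; it establishes only that its two sizes disagree. This stands.
- **20 per group is an inference.** The abstract prints only 60. Equal allocation is the natural reading, and the sample size section assumes equal sizes, but the ratio is not stated. This affects the wording and not the contradiction, since no split of 60 satisfies 26 in each group.
- **The power figures rest on a number that cannot be checked.** They assume that 26, with or without the 5% correction, is the right size for 80% power under the standard two-mean formula. This stands.
- **A larger loss is tempting but not supported.** The analysis section plans Tukey comparisons after ANOVA, and a reader might charge the whole Tukey-adjusted shortfall to the missing 18 participants. But the calculation uses Z = 1.96 with no adjustment, and Tukey-adjusted power would be only about 66-70% even at 26 per group. Much of that shortfall would be there with 78 enrolled, so it is a separate matter and does not measure this one.

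**Conclusion.** The contradiction is certain: 3 × 26 = 78, not 60, and nothing in the article reconciles the two. It does not depend on the missing effect size.

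The consequence for power is conditional. It requires that 60 is the operative size, that it is divided equally, and that 26 is the correct size for 80% power. Under those conditions the unadjusted pairwise power is about 69%, or about 71-72% if 26 already contains the 5% correction. The chance of missing the planned difference rises from 20% to about 28-31%. If 78 is the operative size, the stated power is untouched and only the abstract is wrong. In either case a headline figure is wrong as printed and has to be corrected.

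**What to change.** State one total enrolment, with the size per group, in both the abstract and the sample size section, and check that the flowchart agrees.

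- If 78 is the operative size, correct the abstract.
- If 60 is the operative size, replace the power of 0.80 with the power that 20 per group gives for the planning difference. This should come out at about 69-72%, but the sponsor should recompute it from its own mean difference and variances. Alternatively, keep 80% power and state the larger detectable difference, about 0.89 SD.

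In either case, say whether 26 is before or after the 5% correction.

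The cost is a change of wording. Restating the power or the detectable difference needs no extra participants, though if 60 stands the published figure becomes less favourable. If 78 is meant, the recruitment target has to be 78.
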